#### Tertiary outcome

Participants’ demographic data will be collected and analysed to compare the distribution between control and intervention groups in terms of: age, gender, postcode and highest level of education achieved. The latter two are of particular relevance as the study will assess self-education and disease awareness [15]. The control and intervention groups will also be stratified by disease diagnosis (OHT, SG and COAG), although the aforementioned primary and secondary outcome measures are based on collective data.

Other potential confounding factors that will be recorded for each participant are related to general eye health and the resulting management of the newly diagnosed glaucoma. It will be recorded if patients: have never worn glasses/lenses, wear glasses/lenses due to old age (reading and/or driving), wear glasses since childhood or early adulthood due to congenital visual defect. Note will also made whether patients are prescribed IOP-lowering eye drops or undergo a laser or surgical intervention during the study period.

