**Methods/Design:**

HOPE Glaucoma is a 3-year, prospective, parallel-group, pragmatic, single-centred, randomised controlled trial. An anticipated 122 adults, newly diagnosed with glaucoma (including ocular hypertension, suspected glaucoma and/or chronic open-angle glaucoma) will be recruited from a nurse-led ophthalmology outpatient clinic at a medium-sized NHS Trust. Participants will be randomly allocated to receive standard clinical care (control arm) or standard care plus a glaucoma personal record, detailing the current state of their condition (interventional arm). Participant assessments are designed to test whether provision of a glaucoma personal record 1) improves patient knowledge of glaucoma and 2) contributes to improvements in clinical outcomes, i.e. delay of visual field loss. The primary outcome measure is better client knowledge of glaucoma at the 9–12 month follow-up visit. Secondary outcome measures include the rate of visual field loss and patient-reported outcome measures on visual function (National Eye Institute VFQ – 25) measured at baseline, 9–12 months, 24 months and 36 months. Estimating a 20 % drop-out rate, the study will have 90 % power to detect a mean two-point difference in glaucoma knowledge score between groups at 5 % significance - based on two-sided Mann–Whitney *U* test.

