### Inclusion criteria

Adult (age ≥18 years)Patients newly diagnosed with glaucoma, to include the following three presentations:o ocular hypertension (OHT): intraocular pressures (IOPs) above the normal range (more than or equal to 21 mmHg), but no signs of optic nerve fibre loss or visual field losso suspected glaucoma (SG): optic nerve fibre loss or visual field loss or both in presence of normal intraocular pressureso chronic open-angle glaucoma (COAG): any combination of raised intraocular pressures, optic nerve fibre loss and/or visual field loss.o any combination of the above OHT, SG, COAGBoth primary (cause of outflow resistance or angle closure is unknown) and secondary (outflow resistance results from another disorder) glaucoma cases can be included such as pigment dispersion syndrome (PDS) or pseudoexfoliative glaucoma (PEXF)

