### Sample size

The anticipated patient sample size of 122 will be recruited over a 12-month period. Power calculations for sample size, 90 % power and 5 % significance, based on two-sided Mann–Whitney *U* test for the primary outcome measure, patient knowledge of glaucoma. A priori power calculations, using GPower 3.1 software, result in the following sample sizes summarized in Table 2. The calculation also takes into account a 20 % drop-out rate over the initial 9–12-month follow-up period before patients return for their regular glaucoma follow-up and knowledge questionnaire visit.

**Table 2 Tab2:** Sample size calculation

Mean score control group (± SD)	Mean score intervention group (± SD)	Required total sample size, n
7 (3)	8 (3)	400 (200 per group)
7 (3)	9 (3)	122 (61 per group)
7 (3)	10 (3)	58 (29 per group)

*SD* standard deviation

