### Objective

This study aims to assess whether patient education, through the provision of a glaucoma personal record, results in increased knowledge of their condition and whether this contributes to positive behavioural change and a reduction in the rate of visual field loss. The null hypothesis is that a patient-specific glaucoma personal record has no effect on client knowledge of glaucoma (OHT, SG or CAOG), quantified using a validated researcher-conducted survey at 9–12 months post-recruitment.

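### The between-arm visual-field test is unadjusted although randomisation is unstratified and baseline diagnosis and mean deviation (MD) are collected; the diagnosis categories also overlap

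*Protocol article*

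**What the plan says.** All references are to the protocol article.

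- **Objective.** Beyond knowledge, the trial asks whether the record contributes to "a reduction in the rate of visual field loss". Secondary outcomes makes that rate the longer-term outcome, measured by MD.
- **Inclusion criteria.** OHT is raised pressure "but no signs of optic nerve fibre loss or visual field" loss. SG is "optic nerve fibre loss or visual field loss or both in presence of normal" pressures. COAG is "any combination of raised intraocular pressures, optic nerve fibre loss and/or visual field loss". A further line admits any combination of the three.
- **Randomisation.** Allocation is 1:1, with neither stratification nor blocking.
- **Tertiary outcome.** The arms will be broken down by the three diagnoses, "although the aforementioned primary and secondary outcome measures are based on collective data".
- **Data analysis.** Visual field at baseline and at 36 months is compared within arms by paired tests. Between arms, a t test or Mann–Whitney test is used, depending on a normality test. Neither has a term for diagnosis or baseline MD.
- **Sample size.** The calculation concerns the knowledge score only. No target effect, SD or power is given for visual field.

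**The concern.** Patients enter at very different points. By definition, an OHT patient has an intact field on entry, while others already have loss. If starting field or diagnosis predicts later change, three things follow from an unadjusted test.

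1. Predictable differences between patients stay in the error term and widen the interval for the arm difference.
2. Randomisation does not force the case mix to match, and nothing in the analysis corrects a mismatch that arises by chance.
3. A null result is ambiguous. It could mean that the record does not slow loss, or that too few patients had established loss for slowing to show.

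The breakdown by diagnosis might help with the third, but as defined it cannot be reproduced, because one patient can fit two categories and a mixed patient has no category. Visual field is the trial's main clinical outcome, so a null here is likely to be quoted.

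**Working it through.** **The plan's own figure.** The article states "Power calculations for sample size, 90 % power and 5 % significance, based on two-sided" Mann–Whitney test, for a difference of 2 points with SD 3, so d = 2/3. Noncentral-t power with the Mann–Whitney efficiency 3/π gives 51 per arm. Then 2 × 51 × 1.2 = 122.4, which matches the stated 122. The figure reproduces, but it says nothing about visual field.

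**What the documents do not give.** The share of each diagnosis, MD slope by diagnosis, SD of slope, any target effect on the field, and drop-out to 36 months. The 20% drop-out covers only the first 9–12 months. Everything below is therefore illustrative. It uses 61 × 0.8 ≈ 49 per arm, which may be optimistic at 36 months.

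**Variance left in the error term.** Assume a share π of 30% to 50% in the slower-losing group, a slope gap of 0.3 to 0.5 dB/year, and a within-group SD of 0.5 to 0.8 dB/year. Then R² = π(1−π)gap² / [π(1−π)gap² + SD²].

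- Low end: 0.3 × 0.7 × 0.3² = 0.0189; 0.0189 / (0.0189 + 0.64) = 0.03.
- High end: 0.5 × 0.5 × 0.5² = 0.0625; 0.0625 / (0.0625 + 0.25) = 0.20.

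Adjusting for diagnosis would cut the residual variance by about 3% to 20%. Baseline MD could add to this, by an amount the documents do not allow one to estimate.

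**Chance imbalance.** The standard error of the between-arm difference in share is √[π(1−π) × 2/49], which is 0.093 at π = 0.3 and 0.101 at π = 0.5. Multiplying by 1.96 gives differences of 18 to 20 percentage points within the 95% range. With a gap of 0.3 to 0.5 dB/year, that shifts the unadjusted arm difference by 0.18 × 0.3 = 0.05 up to 0.20 × 0.5 = 0.10 dB/year.

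**Reading a null.** Suppose, as an extreme case, that a share f of patients contributes no effect at all and the rest have a standardised effect of 0.8. The pooled effect is (1−f) × 0.8. At equal SD, noncentral-t power is:

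| f | Pooled, 49 per arm | Patients with loss only, 49(1−f) per arm |
|---|---|---|
| 30% | 78% | 90% |
| 50% | 50% | 78% |

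With an effect of 0.6, the pairs are 54% v 69% and 31% v 54%. This shows only why a supportive analysis would help interpretation. It does not estimate what this trial will lose.

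**Overlap of categories.** No assumption is needed here. A patient with normal pressure and both nerve and field loss meets SG and, read literally, COAG. A patient with raised pressure alone meets OHT and, on the same literal reading, COAG. A patient admitted under the combination line belongs to none of the three groups on its own.

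**The case against.** The strongest reply is that pooling is deliberate. The Background defines the trial question for OHT, SG and COAG together, and the pooled arm difference is an unbiased estimate for that population. This stands, and the pooled estimate should stay.

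A reader might infer something stronger: that OHT patients have nothing to lose, so pooling necessarily dilutes the effect in proportion to their share. The documents do not support that. OHT patients lack loss only at entry, and intact fields can be lost over 36 months. The article itself calls raised pressure a major risk factor. Nor is the OHT share the no-loss share: SG can be nerve fibre loss alone, and COAG need not include field loss.

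A reader might also infer that the plan ignores diagnosis altogether. It does not, because the arms are to be broken down by it. What is missing is any role for diagnosis in the visual-field test.

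It can be said too that covariates are commonly left to an analysis plan. Here, though, the article names the tests and states that the outcomes are pooled, so the choice has been made.

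Finally, the magnitudes are assumed and the outcome is secondary with no power calculation. Both points are right and limit the weight of the concern. At the low end, 3% of variance is negligible.

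**Conclusion.** The point holds as one of efficiency and interpretability, not of bias. The plan fixes an unadjusted between-arm test after unstratified randomisation, although two baseline variables likely to predict the outcome are available. The gain from using them cannot be derived from the documents. Under the assumptions shown, diagnosis alone accounts for 3% to 20% of the variance, and a chance imbalance could move the unadjusted difference by 0.05 to 0.10 dB/year. The power comparison assumes no effect in one group, an effect of 0.6 or 0.8 in the other, equal SDs and 49 per arm, so it cannot be read as the trial's actual loss of power. Adjustment does not undo dilution; only the supportive analysis speaks to that.

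The overlap between categories is established from the text. It leaves eligibility and the pooled tests untouched, but it would undermine any use of diagnosis in an analysis or a table. The change is worth making, but the primary outcome does not depend on it.

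**What to change.** 1. In Data analysis, keep one pooled all-patient estimate, but obtain it from a regression of visual-field change (or MD slope) on arm, adjusted for baseline MD and baseline diagnosis group. This replaces the unadjusted between-arm t test or Mann–Whitney test.
2. Beside it, pre-specify the arm difference in patients with field loss on the baseline test, labelled supportive. Baseline field status is a better basis than the diagnosis label, since SG and COAG patients may also enter without field loss.
3. In Inclusion criteria and Tertiary outcome, reconcile the OHT, SG and COAG definitions, including the combination line, so that each patient falls in exactly one analysis category. Trial status reports 85% of the sample already recruited, so for those patients the category cannot be recorded before allocation. Assign it from baseline records without reference to arm.

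The cost is a change of analysis wording and one recoded baseline variable from data already collected. No visit, test or aspect of care changes. The downside is the supportive analysis, which has fewer patients and lower precision and should not be read as a second chance at significance.

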### Data collection and monitoring

Participant follow-up will be 3 years. The estimated primary completion date is September 2015 and the estimated study completion date is September 2017. An overview of the study timeline and recorded outcome measures are detailed in Table 4. Outcome data will be collected during clinically scheduled ophthalmology outpatient appointments with the CI and subjects will not be asked to attend any additional clinic appointments above those required for their clinical care. This design was used to increase the pragmatism of the study and improve subject retention throughout the duration of the study. Outcome data will not be collected for patients that withdraw from the study or deviate from the study timeline.

**Table 3 Tab4:** The scoring system used to establish participants’ knowledge of glaucoma and its management. Source: [9]

Number	Question	Scored 0	Scored 1	Scored 2	Scored 3	Max score
1	Can you tell me what you think glaucoma is?	Don’t know/ incorrect answer	Build up of pressure, raised/high pressure, nerve damage, loss of vision	Optic nerve damage, irreversible vision loss, chronic disease, slowly progressive (in own words)	NA	2
2	Can you tell me which part of the eye can become damaged with glaucoma?	Don’t know/ incorrect answer	Back of the eye	Retina	Optic nerve	3
3	Can you tell me what effect glaucoma has on vision if left untreated?	Don’t know/ incorrect answer	You go blind/you gradually go blind/ you lose vision	You get tunnel vision	NA	2
4	Can you tell me what part of vision glaucoma affects the most?	Don’t know/ incorrect answer	Visual field/field of vision/side vision	NA	NA	1
5	Is glaucoma hereditary/does glaucoma run in families?	No/don’t know	Yes	NA	NA	1
6	Do you know what investigations/tests will be carried out regularly at future clinic appointments to monitor changes in your eyes?	Don’t know/ incorrect answer	Either IOP measurement, visual field test or optic nerve examination (in own words)	Any two of the tests (in own words)	All three tests (in own words)	3
7	Do you know the name(s) of the drop(s) that has/have been prescribed for you?	Don’t know/ incorrect answer	Yes (client named the drops)	NA	NA	1
8	Do you know what the drops do?	Don’t know/ incorrect answer	Lower/reduce/control eye pressure	NA	NA	1
9	Do you know when you will need to collect your next prescription?	Don’t know/ incorrect answer	1 month/28 days	NA	NA	1

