### Outcome measures

#### Primary outcome

The primary outcome measure is client knowledge of glaucoma, quantified using a validated researcher-conducted survey at 6–12 months post-recruitment [8], see Table 3. This survey and scoring system was used, and validated by ophthalmic colleagues in 2009/2010 “to establish the impact of educational support on clients’ knowledge of glaucoma and adherence, in preparation for a further interventional study” [9]. It provides an ordinal score of participants’ knowledge. The primary outcome measure is therefore the degree of understanding and knowledge retention of their OHT, SG, or COAG in the interventional group compared with the control group. Patients requiring ocular antihypertensive treatment at first presentation are eligible for inclusion in this trial; the total knowledge score achievable is either 12 for those not prescribed antihypertensive drops, or 17 for those prescribed eye drops during the course of the study. The survey will be administered by the CI when participants attend a ‘glaucoma review’ outpatient clinic between 6 and 12 months post-recruitment.

**Table 4 Tab3:** Overview of study timeline and outcome measures

Baseline	Baseline	9–12 months	24 months	36 months
Patient knowledge		X		
Patient perspective (VFQ-25)	X	X	X	X
Clinical parameters	X	X	X	X

*VFQ-25* National Eye Institute Visual Functioning Questionnaire – 25

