The impact of visual field loss on patients’ lives will be measured using the vision-targeted health-related quality of life (HRQOL) measure: the National Eye Institute Visual Functioning Questionnaire – 25 (VFQ-25). This validated patient-reported outcome measure tool was designed to measure the impact of visual deficit on physical functioning, emotional well-being and social functioning [14]. The VFQ-25 will be completed by participants attending the CI’s nurse-led glaucoma review outpatient clinic at baseline, 6–12 months, 24 month and 36 months post-recruitment.

The patient glaucoma record will use ‘traffic light’ graphs to make it more straightforward for patients to see the status of their glaucoma for e.g. visual field loss [11]. A copy of the patient glaucoma record is available (Additional file 1).

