### Data analysis

Patient eligibility, recruitment and retention through the study will be presented in a CONSORT flow diagram displaying the number of eligible patients, patients approached with study information, patients recruited and randomised and patients completing study follow-up. Reasons for loss to follow-up will also be presented, where known. Participant baseline details and descriptive statistical data will be tabulated to show overall recruit demographics, and any differences in distribution (e.g. patient age, sex, level of education) will be analysed by applying one-way ANOVA or chi-squared test.

The primary outcome, the degree of difference in patient knowledge about their glaucoma condition will be analysed by comparing the average scores for control patients versus the average score of patients received the glaucoma personal record. Statistical significance will be assessed by applying the Mann–Whitney *U* test. The secondary outcome, visual field loss, will be measured with a Humphrey Automated Visual Field Analyser in the ophthalmology clinic and average measurements for baseline visit and the final visit at 36 months will be compared within each group (control and intervention respectively) and also between the two groups. Depending on distribution of the data, determined by Shapiro-Wilk test, the paired *t* test or Wilcoxon test will be applied for paired samples to determine any significant changes in visual field loss. For assessing differences between the control and intervention groups, either *t* test or Mann–Whitney *U* test will be applied. Like visual field loss, the other secondary outcome measure - patient-related outcome measure VFQ-25 - will be presented as average scores. Any statistical differences will be assessed by Wilcoxon test within each group and Mann–Whitney *U* test between groups.

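### Outcomes are not collected from participants who go off the study timeline, and that timeline gives the primary visit as both 9–12 and 6–12 months

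*Protocol article*

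**What the plan says.** **The collection rule.** The Data collection and monitoring section states that "Outcome data will not be collected for patients that withdraw from the study or deviate from the study timeline". The same section ties outcome collection to routine appointments: "subjects will not be asked to attend any additional clinic appointments above those required for their clinical care". It refers to Table 4 for the timeline.

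**The primary window, 9–12 months.**
- Abstract, Methods/Design: "The primary outcome measure is better client knowledge of glaucoma at the 9–12 month follow-up visit".
- Objective: the null hypothesis concerns knowledge "quantified using a validated researcher-conducted survey at 9–12 months post-recruitment".
- Background, Sample size and Table 4 give the same window.

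**The primary window, 6–12 months.**
- Primary outcome: knowledge is "quantified using a validated researcher-conducted survey at 6–12 months post-recruitment", and the survey is given at a review clinic "between 6 and 12 months post-recruitment".
- Secondary outcomes: the VFQ-25 is completed "at baseline, 6–12 months, 24 month and 36 months post-recruitment", whereas Table 4 and the abstract place its first follow-up at 9–12 months.

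**Design of the outcome.** The Consent section describes a post-test-only design, and Table 4 shows knowledge measured at one visit only.

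**The concern.** Taken alone, the two windows could be a drafting slip. Combined with the collection rule, they decide who has a primary outcome.

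The rule governs collection, not analysis, so it is not a detail that a later analysis plan can settle. A score that was never taken cannot be restored, and without a baseline knowledge score there is little from which to model it.

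The comparison could then be confined to participants who stayed in the study and attended on time. That is a status reached after randomisation. Visits follow clinical scheduling, and Secondary outcomes allows more frequent field testing when clinically indicated, so timing may carry information about disease status. The Background expects the record to engage patients more, so timing may also differ between arms. At stake is whether the groups compared are still the groups that were randomised.

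**Working it through.** **1. Who is affected by the two windows.**

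| Only survey visit falls at | Under 9–12 months | Under 6–12 months |
|---|---|---|
| 6 to under 9 months | off timeline | on time |
| 9 to 12 months | on time | on time |
| after 12 months | off timeline | off timeline |

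The first row depends on which statement is followed. The third row loses its outcome under either, if the rule is applied literally. The planned dates do not settle the matter: a last recruit in September 2014 (Trial status) plus 12 months gives September 2015, the stated primary completion date. Both windows share that upper limit.

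**2. The plan's own figure.** Inputs from Sample size: means 7 and 9, SD 3, two-sided 5%, 90% power, 20% drop-out, 122 in total. The standardised difference is 2/3 = 0.667.
- Mann–Whitney, using efficiency 3/π relative to the t test: 51 per arm; 51 × 1.2 = 61.2, so about 61 per arm and 122 in total. Dividing by 0.8 instead gives 63.75, so 64 per arm and 128.
- t test: 48.26 / 0.8 = 60.3, so 61 per arm and 122.

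The figure reproduces under ordinary variants, and the sample size arithmetic is not in question.

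**3. Precision if more outcomes are lost.** With 61 per arm and loss d, the effective size per arm is m = 61 × (1 − d) × 3/π and the noncentrality is 0.667 × √(m/2). At d = 0.20: 61 × 0.8 = 48.8, m = 46.6, noncentrality 3.22, power 89.0%. Loss rates above 20% are assumptions.

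| Loss | Mann–Whitney power |
|---|---|
| 0% | 94.6% |
| 20% | 89.0% |
| 30% | 84.5% |
| 40% | 78.4% |

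The 20% is described as drop-out; off-timeline exclusions are not mentioned separately. These figures hold only if loss is unrelated to score.

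**4. Bias, as illustration only.** If a share f of an arm is excluded and those excluded score D points below those kept, the observed mean is too high by f × D. The error in the difference (intervention minus control) is (f_I − f_C) × D. No value of f or D is in the documents.
- Assume 30% of controls and 10% of intervention patients are excluded, with D = 2 to 3. The control mean rises by 0.6 to 0.9 and the intervention mean by 0.2 to 0.3. The error is −0.4 to −0.6 points, so the benefit is **understated** by 20–30% of the two-point target.
- Exchange the two shares and the error is +0.4 to +0.6 points, so the benefit is **overstated**.
- Equal loss does not guarantee safety. A simulation (4,000 trials per setting) assumed no true effect, 61 per arm and 20% missing in each arm. Loss was unrelated to score in control. In intervention, the log-odds of being observed rose by 0.5, 1 or 2 per SD of score. The spurious difference was about 0.3, 0.5 or 0.8 points, and the two-sided type I error about 8%, 12% or 25%. With no dependence on score the error was 4.9%.

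The sign and size therefore follow from the assumptions, not from the protocol.

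**The case against.** Several points on the other side are fair.

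- **The rule is not defined closely.** Deviating from the timeline could mean missing follow-up altogether rather than attending a few weeks late, in which case little obtainable data would be lost. A participant first reviewed at month 7 may also be seen again by month 12. This stands as a limit on the number affected. It also shows why the rule needs rewording, since its plain text covers late attenders.
- **Timing may reflect clinic scheduling only.** Appointments are set clinically, and the documents do not show that early or late attendance tracks engagement or severity. This stands: the loss may be informative, but that is not established.
- **Stopping collection on withdrawal can be proper.** It depends on consent documents that are not shown. This stands. The clear defect is the rule for timeline deviators, together with the failure to distinguish withdrawal from the study from withdrawal of consent for data.
- **Losses will be visible.** Data analysis promises a CONSORT diagram with reasons for loss where known. That makes losses visible but does not recover the scores.

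Two stronger readings may tempt a reader. The first is that the wording "versus the average score of patients received the glaucoma personal record" signals an as-treated analysis. It does not: Randomisation and Intervention description have the record handed over immediately after consent, so allocation and receipt practically coincide, and Primary outcome compares the two groups as such. The second is that the unmasked chief investigator will decide who is off timeline. The Discussion does acknowledge an unmasked assessor, but no passage says who applies the rule.

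**Conclusion.** The concern holds in this form: the protocol has a stated rule against collecting outcomes from off-timeline participants, and it defines the timeline of the primary visit in two incompatible ways. Followed as written, the plan gives up primary outcomes that could be obtained at routine visits, and they cannot be recovered later.

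The size is unknown. The documents give no count of off-timeline participants and no basis for a direction of bias. A reader might infer that the rule favours the record. The documents do not support that, and the scenario with more exclusions among lower-scoring controls makes the record look worse. The only consequence that follows without assuming score-related loss is reduced precision if total loss exceeds the 20% allowed.

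**What to change.** 1. Choose one window for the primary visit and use it in the abstract, Background, Sample size, Objective, Primary outcome, Secondary outcomes and Table 4. The sponsor should decide which was intended.
2. Replace the off-timeline rule: give the survey at the review visit within the window or, if there is none, at the nearest later routine review. Do not give it before the window's lower limit. An early survey would change an outcome meant to capture knowledge retention, and would do so more often in patients reviewed more frequently.
3. Continue VFQ-25 and visual field collection at later routine visits after a missed or late one. Stop only when the participant withdraws consent for data.
4. Include every collected outcome in the group as randomised.
5. Record actual months since randomisation, and run a within-window-only sensitivity analysis.

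**Cost.** This is a wording amendment to an ethically approved protocol, made while recruitment stands at 85%. No visits are added. Survey dates will spread more widely, which the sensitivity analysis addresses. A few late surveys may fall after the estimated primary completion date of September 2015, but participants are followed for 3 years in any case.
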